### Sample size estimate

This study is a pilot study, which is planning to recruit 150 patients. This sample size is a justification from statistical considerations as follows:

The hypothesis on the primary endpoint is to test the mean amplitude of glycemic excursion (MAGE) in exenatide group superior to aspart 30 group. According to the literature review and previous studies, the standard deviation (SD) of change of MAGE is conservatively estimated as 3.0 mmol/L (in a pilot study of exenatide, the SD of MAGE is 2.7 to 3.1 mmol/L) [17]. With a two-sided 0.05 alpha level and a 15 % dropout rate, 150 patients with a 1:1 allocation rate (75 patients per group) will offer at least 85 % power to test a minimum 1.6 mmol/L difference on the change of MAGE between the exenatide and aspart 30 groups.

### Assignment of interventions

Patients will be randomized 1:1 to treatment groups via a central randomization system (interactive voice/web response system (IVRS/IWRS)), and the drug will be dispensed accordingly. The study population will be stratified at randomization based on MAGE (<5.6 mmol/l and ≥ 5.6 mmol/l) and the severity of the disease (HbA1c < 9.0 % and ≥ 9.0 %).

Because the study drug (Exenatide) has an obviously different appearance from, and is used differently from, the biphasic insulin aspart 30, a definite blindness is hard and worthless for investigators and patients. Therefore, an open-label study is being conducted. Bias at randomization is reduced by the use of a central randomization system. Moreover, key efficacy parameters (MAGE, HbA1c, FPG, and postprandial plasma glucose (PPG)) will be blinded for the investigator during the course of the study (from randomization to week 16) except for the screening and pre-randomization visit. However, when FPG meets the study drug discontinuation criterion of hyperglycemia, the investigator will be alerted to conduct retest for confirmation.

### Data collection and management

The laboratory parameters that will be measured to assess efficacy and safety at each visit are shown in Table 3. Blood samples for efficacy and safety assessments will be performed on the days of the specified visits in a fasted condition (expect 2-h PPG), prior to administration of study treatment (patients must not take study drug at home on the day of the study visit but must bring it to the study center). Blood sample for 2-h PPG testing will be drawn at 120 min after the first intake of standard meal during the standard meal testing on the days of the specified visits. All blood samples for efficacy assessments in the study will be sent to the central lab for analysis. The blood and urine samples for safety assessments will be performed at local laboratories.

Blood glucose (BG) is monitored in the study sites by a Guardian™ Real-Time CGMS (Medtronic MiniMed Inc., CA, USA), which is used to record glucose levels every 5 min for 72 h consecutively. During the second visit (baseline visit) and the last visit (end of the study), the continuous glucose sensor is inserted subcutaneously in the abdominal periumbilical area, separately. Meanwhile, a blood glucose meter is used to perform sensor calibration four times daily. The participants receive a calibration 2 hours after sensor insertion and then four glucose calibrations at each meal and before bed, and the time of each meal is marked in the consecutive 3-day test. Participants are provided the same mixed meals (30 kcal/kg ideal weight/day, based on dietitian recommendations, including 55 % of calories from carbohydrates, 25 % from fat and 20 % from proteins, with a meal distribution of 1/5, 2/5 and 2/5). They must keep a diary of meals (content and times) and avoid intensive physical activity during both CGMS periods. The dietary pattern using 3-day diet records for each CGMS study period will be checked in all participants. All the parameters of continuous glucose monitoring are calculated from each CGMS output, which is extracted using the CGMS 3.0 software package (Medtronic MiniMed, MMT-7310 version 3.0C (3.0.128), CA, USA). The mean glucose level is calculated as the mean of all the consecutive sensor readings, from which the SD is also calculated. The largest amplitude of glycemic excursion (LAGE) is defined as the maximal sensor glucose level minus the minimal sensor glucose level during each day. The MAGE is used for assessing the intraday glucose variability. MAGE is calculated by measuring the arithmetic mean of the differences in consecutive peaks and nadirs, which are taken into consideration only if they exceed one standard of deviation from the mean [18]. The mean of the daily differences (MODD), calculated as the average absolute difference of paired sensor glucose values during two successive 24-h periods, is used to assess the interday glucose variability.

Instant noodles are used as a standard meal, which includes 85 g of instant noodle equivalent to an energy intake of 500 kilocalories. The procedures for standard meal test are described in Table 4. The fasting plasma glucose will be tested at visits 1 to 6. HbA1c, fasting C-peptide and 2-h PPG will be tested at visit 1, 2 and 6. The baseline is defined as the assessment at Visit 2. The samples are collected after fasting for 12 hours for fasting plasma glucose, fasting C-peptide and HbA1c. Then the participants will be given 85-gram instant noodles and asked to eat up in 8 minutes at visit 2 and visit 6. Two hours later, blood samples will be collected again for plasma glucose.

**Table 4 Tab4:** Overview of standard meal test assessments

Time	Assessment
-15 ± 5 min	Blood sampling for plasma glucose, insulin, and C-peptide testing
-15 ± 5 min	Administer metformin and exenatide (or biphasic insulin aspart 30)
0 min	Start of ingestion standard meal
+8 ± 2 min	End of ingestion standard meal
+120 ± 10 min	Blood sampling for plasma glucose, insulin, and C-peptide testing

All time points are relative to targeted first mouthful of the standard meal, at Time 0

Physical examination, electrocardiogram, vital signs, and other safety assessments also will be performed using standard methods. Since the two study drugs (exenatide and biphasic insulin aspart 30) are two well-described safe antihyperglycemic medications, and our treatment period is only 16 weeks, some of the safety assessments, like urinalysis, liver function, creatinine, and blood urea nitrogen, are tested only at the baseline and the 16-week safety assessment. Adverse events during all the study period will be collected.

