### Interventions

The trial will include a 1-week screening period of stable doses of metformin (1500 mg) and a 16-week treatment period. Patient will take the first dose after randomization on Day 1. The investigational products of exenatide and biphasic insulin aspart 30 will be administered through subcutaneous injection. The background product of metformin will be taken orally at 500 mg three time daily until the completion of the study.

Exenatide (AstraZeneca) should be initiated, 60 minutes before breakfast and before dinner, at a low dose of 5 ug twice a day for 4 weeks and then titrated up to a standard dose of 10 ug twice a day until the completion of the study.

Biphasic insulin aspart 30 (Novo Nordisk) will be started at a dose of 0.2 to 0.4 IU/kg, or 10 to 12 IU/d, assigned to before breakfast or before dinner in a 1:1 ratio. The adjustment of the insulin dose will be instructed to achieve an optimal balance between glycemic control and the risk of hypoglycemia as dictated by clinical practice. It will be titrated to glucose targets of fasting plasma glucose (FPG) and predinner plasma glucose < 7 mmol/L. Insulin dose titration will be based on the average self-monitored blood glucose (SMBG) results for 3 days preceding visits, unless hypoglycemia occurs. If hypoglycemia occurs, titration will be temporarily postponed, and the reasons of hypoglycemia will be evaluated. Subjects could not increase the total daily dose by more than 10 U at any time. After visit 2 (week 0), insulin doses will be titrated weekly for the first 12 weeks, then every 2 weeks thereafter according to the titration algorithm (Table 1).

**Table 1 Tab1:** Prebreakfast and predinner insulin titration regimens

Fasting and/or predinner SMBG PG value (mmol/L)	Adjustment
<5.0	-2 U
5.0 to 7.0	No adjustment
7.1 to 7.7	+2 U
7.8 to 10	+4 U
>10	+6 U

BG, blood glucose; SMGB, self-monitored blood glucose

Glycemic targets for titration: Prebreakfast and predinner PG: 5.0 to 7.0 mmol/L. Prebreakfast dose of biphasic insulin aspart 30 is titrated based on the three mean predinner PG values for the 3 days prior to the visit. Predinner dose of biphasic insulin aspart 30 is titrated based on the three mean fasting PG values for the 3 days prior to the visit. The predinner biphasic insulin aspart 30 titration is not increased if the preceding day’s bedtime SMGB value is 5.6 mmol/L

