### Participant timeline

The time schedule for the enrollment, interventions, assessments, and visits for participants are shown in Table 3.

**Table 3 Tab3:** Study plan detailing the procedures

Study Period	Screening	Treatment							
Visit	V1	V2	V3	V4	V5	V6	V7	V8	V9
		Randomization							
Week	−1	0 (baseline)	1	2	4	8	10	12	16
Day		0	±2	±2	±7	±7	±2	±7	±7
Telephone visit			×	×			×		
Screening/baseline									
Written informed consent	×								
Inclusion/exclusion criteria	×	×							
Demographics	×								
Physical examination	×	×			×	×		×	×
Medical/current conditions	×	×	×	×	×	×	×	×	×
History of diabetes & complications	×								
Lifestyle instruction	×	×	×	×	×	×	×	×	×
Treatment									
Drug dispensing and accountability		×			×	×		×	
Concomitant medications	×	×	×	×	×	×	×	×	×
SMBG			×	×	×	×	×	×	×
Insulin titration			×	×	×	×	×	×	
Safety assessments									
Pregnancy test (urine)	×								×
Physical examination	×	×			×	×		×	×
Vital signs	×	×			×	×		×	×
12-lead ECG	×								×
Hematology panel	×								×
Urinalysis	×								×
Liver function	×								×
Creatinine, BUN, uric acid	×								×
Lipids	×				×				×
Adverse events		×	×	×	×	×	×	×	×
Efficacy assessments									
HbA1c	×								×
Fasting plasma glucose	×	×			×	×		×	×
Fasting insulin and C-peptide		×							×
CGMS		×							×
Standard meal test:2 h PPG, insulin and C-peptide		×							×
BW, BMI and WC	×	×			×	×		×	×
Other assessment									
MCP-1, hs-CRP		×							×
8-Iso-PGF2α		×							×
Urinary albumin		×							×

SMBG, self-monitoring of blood glucose; ECG, electrocardiogram; BUN, blood urea nitrogen; CGMS, continuous glucose monitoring system; PPG, postprandial plasma glucose; BW, body weight; BMI, body mass index; WC, waist circumference; MCP-1, monocyte chemotactic protein-1; hs-CPR, high-sensitivity C-reactive protein; 8-Iso-PGF2α, 8-Iso-prostaglandin F2α

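### The 72-hour baseline CGMS recording starts at the randomisation visit, so the MAGE needed for stratification cannot exist yet; the final recording likewise starts at the last visit

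*Protocol article*

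**What the plan says.** All references are to the protocol article.

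- **Data collection and management:** the monitor is used to "record glucose levels every 5 min for 72 h consecutively". On timing, "During the second visit (baseline visit) and the last visit (end of the study), the continuous glucose sensor is inserted subcutaneously". The same section defines baseline as the Visit 2 assessment and places a standard meal test at that visit. Table 4 lists, before the meal, "Administer metformin and exenatide (or biphasic insulin aspart 30".
- **Participant timeline, Table 3:** V2 carries the randomisation label, week 0, Day 0 and no window. CGMS is marked at V2 and V9 only. V9 (week 16, ±7 days) is the last column. Drug dispensing is marked at V2, V5, V6 and V8, not at V9.
- **Assignment of interventions:** "The study population will be stratified at randomization based on MAGE (<5.6 mmol/l and ≥ 5.6 mmol/l", together with HbA1c at 9.0 %.
- **Interventions:** "Patient will take the first dose after randomization on Day 1". The same section confirms that V2 is week 0: "After visit 2 (week 0), insulin doses will be titrated weekly for the first 12 weeks".
- **Outcomes, Table 2:** the primary outcome is the absolute change in MAGE from baseline to week 16.

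**The concern.** MAGE can be computed only after the recording has run. A stratification factor must be known before the allocation is drawn, and a baseline must be complete before treatment starts. A recording that begins at the randomisation visit meets neither condition if the other stated dates are kept.

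Two things are at stake. One is whether the stated stratified randomisation can be carried out at all. The other is whether the baseline half of the primary outcome is a pre-treatment measurement. In a multicentre trial, sites could also resolve the conflict differently, so that some baselines are drug-free and others are not.

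The final recording raises a related question. If it starts at the last visit, it describes the three days after that visit, and the schedule shows no contact during or after it.

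**Working it through.** **1. Timing at baseline**

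Inputs: insertion at V2 and 72 h duration (Data collection and management); V2 = randomisation = Day 0 (Table 3); first dose on Day 1 (Interventions); MAGE stratum at randomisation (Assignment of interventions).

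- End of recording = Day 0 + 72 h = Day 3.
- The MAGE stratum is needed on Day 0, so it arrives about 3 days too late.
- Hours of the baseline recording after first dose = 72 − lag, where lag is the time from insertion to first dose. The document gives days, not hours, so the lag is assumed:

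| Assumed lag (h) | Hours after first dose | Share of 72 h |
|---|---|---|
| 0 (drug given at the V2 meal test, as Table 4 would imply) | 72 | 100 % |
| 24 (Day 0 to Day 1) | 48 | 67 % |
| 48 | 24 | 33 % |

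No single-day V2 with dosing on Day 1 leaves room for 72 drug-free hours.

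**2. Timing at the end**

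Insertion at V9 + 72 h = three days after the last scheduled contact. Nothing is dispensed at V9. Whether patients take study drug during those hours is not stated.

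**3. The plan's own power figure**

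Inputs (Sample size estimate): SD of change 3.0 mmol/L, difference 1.6 mmol/L, two-sided alpha 0.05, 75 per group, 15 % dropout.

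- n per group = 75 × 0.85 = 63.75.
- Standard error = 3.0 × √(2/63.75) = 0.531; 1.6/0.531 = 3.01.
- Power = 84.8 % (noncentral t) or 85.3 % (normal approximation). The stated 85 % reproduces; the sample size is not in dispute.

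**4. What an on-drug baseline could do (illustration only)**

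Suppose 48 of the 72 h are on drug and those hours show a fraction f of the final 1.6 mmol/L difference. Then the baseline is shifted between arms by dB = 1.6 × f × 48/72. The document gives no value for f, and treating MAGE as proportional to hours is a simplification.

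- An unadjusted change score keeps 1.6 − dB.
- A baseline-adjusted covariance model with slope b keeps 1.6 − b × dB, which is more whenever b is below 1.

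For the adjusted model assume equal SDs at both times and correlation 0.5. Then b = 0.5. The SD at each time is 3.0/√(2 × (1 − 0.5)) = 3.0, and the residual SD is 3.0 × √(1 − 0.25) = 2.60.

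| f | dB | Change score: difference, power | Adjusted: difference, power |
|---|---|---|---|
| 0 | 0 | 1.60, 85 % | 1.60, 93 % |
| 0.25 | 0.27 | 1.33, 70 % | 1.47, 88 % |
| 0.5 | 0.53 | 1.07, 51 % | 1.33, 82 % |
| 0.75 | 0.80 | 0.80, 32 % | 1.20, 73 % |

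With f = 0.5, the adjusted power is about 92 % at correlation 0.3 and 70 % at correlation 0.7. The range is wide because its inputs are assumed. It shows direction under those assumptions; it is not an estimate of the loss in this trial.

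**The case against.** - **An article condenses the procedure.** The blinding text in Assignment of interventions exempts a pre-randomization visit, which hints that MAGE is known before allocation and that V2 may span several days. This is the best counter-argument. If it is so, the stratum can be entered and there is no overlap. But Table 3 shows no separate visit of that kind with CGMS, and Day 0 followed by a first dose on Day 1 leaves no 72 h. The point is also not an omission: insertion visit, duration, randomisation day and first-dose day are all stated, and they conflict.
- **Failed stratification and on-drug baseline are alternatives.** A reader might infer that both occur. That does not follow: if the stratum is taken from the completed baseline recording, that recording ended before randomisation. This objection stands.
- **The loss of power is unproven.** This also stands. No early effect is given, and the Interventions section starts exenatide at the lower of its two doses and titrates insulin over weeks, so nothing in the document supports a large effect within two days. A reader might also suppose that covariance adjustment makes matters worse than a change score. Step 4 shows the reverse for slopes between 0 and 1, and Statistical methods names a covariance model for the efficacy endpoints.
- **The week-16 recording may be on drug.** A reader might conclude that it runs off treatment. The document does not establish that: no text stops drug before the recording, the Interventions section continues exenatide to study completion, and the absence of dispensing at V9 does not show that patients have none left. The ±7-day window also means that the three days after V9 can still count as week 16. What remains is an unstated treatment status, which is a risk and not a demonstrated dilution.

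**Conclusion.** The conflict holds. As written, the insertion visit, the 72 h duration, randomisation on Day 0 with a MAGE stratum, and a first dose on Day 1 cannot all be followed. At least one must give way: the stratum, the stated dates, or a drug-free baseline.

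The firm size is in time: MAGE arrives about 3 days after it is needed, and about 48 of 72 baseline hours follow the first dose if dosing starts 24 h after insertion. This rests on V2 being a single day, as Table 3 shows it. The effect on the treatment estimate arises only in the on-drug case and cannot be quantified from the document. In that case the baseline is a post-randomisation value, and a baseline-adjusted model loses less than an unadjusted change score.

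For the final recording, the established fact is that it runs past the last scheduled contact with treatment status unspecified. It deserves correction because baseline and week-16 MAGE are the whole of the primary outcome.

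**What to change.** 1. Schedule the baseline CGMS recording inside the existing 1-week screening period, so that it is complete and MAGE is computed before randomisation. Enter that MAGE in the IWRS as the stratum.
2. Schedule the final recording to end at V9; its ±7-day window allows this.
3. Correct Table 3 and the CGMS paragraph of Data collection and management to match. Reconcile these with Interventions, Assignment of interventions and Table 4, so that the timing of each recording relative to randomisation, first dose and last dose is stated once and consistently. How the dosing dates are settled is for the sponsor.
4. Trial status says that recruitment has begun. Identify patients whose baseline was recorded under the present schedule, document when their recording ran relative to randomisation and first dose, and examine them in a sensitivity analysis of the primary outcome.

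Cost: a schedule amendment and a sensor-insertion contact before V2 and before V9. The amendment also leaves two baseline procedures within one trial, which is why step 4 is needed.

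### Table 4's study-drug step, read at Visit 2, makes the baseline 2-hour meal-test values post-dose, against other statements about what happens before randomization

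*Protocol article*

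**What the plan says.** All references are to the protocol article.

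- **Procedure.** Data collection and management states: "The procedures for standard meal test are described in Table 4". The table lists a blood sample at -15 ± 5 min, then at the same nominal time "Administer metformin and exenatide (or biphasic insulin aspart 30"), the meal at 0, and a second sample at +120 ± 10 min. Its footnote reads: "All time points are relative to targeted first mouthful of the standard meal, at Time 0".
- **Visits.** Participants are "asked to eat up in 8 minutes at visit 2 and visit 6". Table 3 marks the meal test at V2 and V9, so the final visit is numbered differently, but Visit 2 is a meal-test visit in both places.
- **Baseline.** "The baseline is defined as the assessment at Visit 2".
- **Randomization and dispensing.** Table 3 puts both at V2.
- **First dose.** Interventions says: "Patient will take the first dose after randomization on Day 1".
- **2-h sample.** "Blood sample for 2-h PPG testing will be drawn at 120 min after the first intake of standard meal". The general sampling rule in the same paragraph puts blood draws before study treatment and exempts the 2-h PPG from fasting.
- **Before randomization.** Assignment of interventions calls MAGE, HbA1c, FPG and PPG key efficacy parameters. It keeps them from the investigator except at screening and at a pre-randomization visit. It also stratifies on MAGE, which comes from a 72-h CGMS recording begun at Visit 2.
- **Exenatide timing.** Interventions gives it "60 minutes before breakfast and before dinner"; Table 4 places it 15 ± 5 min before the test meal.

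**The concern.** A baseline value should be measured before any randomized treatment. A site that follows Table 4 at Visit 2 would give the allocated drug and then collect a 2-h value that the protocol calls baseline. Change from that value would leave out whatever the first dose did, in each arm separately. If it entered the covariance model, the covariate would itself be affected by treatment.

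Analysis could not recover the loss, because no untreated 2-h value would exist. The text does list 2-h PPG at visit 1 as well, but no meal is described there and Table 3 shows no meal test at V1.

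Other sections imply that the test comes before randomization, so different sites could reasonably do different things.

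**Working it through.** **The plan's own figure.** The only design calculation concerns MAGE and does not bear on this point. It reproduces: 75 × 0.85 = 63.75 per arm; SE = 3.0 × √(2/63.75) = 0.531; 1.6/0.531 − 1.96 = 1.05; power 0.853, against the stated minimum of 85 %. No figure is given for the meal test.

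**Step 1: timing from Table 4.** The dose falls between -20 and -10 min and the second sample between +110 and +130 min.
- Nominal gap: 15 + 120 = 135 min.
- Shortest: 10 + 110 = 120 min. Longest: 20 + 130 = 150 min.
- The -15 min sample is listed before the dose, and the general sampling rule supports that order. Fasting glucose, insulin and C-peptide are therefore pre-dose.

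**Step 2: the texts side by side at Visit 2.**

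| Text | What it implies for the Visit 2 2-h sample |
|---|---|
| Table 4, no visit exception | after study drug |
| Table 3, randomization and dispensing at V2 | drug could be available |
| Baseline defined as Visit 2 | should be untreated |
| PPG open to the investigator at a pre-randomization visit | measured before randomization |
| Stratification on MAGE from a 72-h recording begun at Visit 2 | allocation not known when the visit starts |
| First dose after randomization, on Day 1 | order relative to the meal test not settled |

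The Day row of Table 3 shows 0 for V2 but otherwise holds visit windows (±2, ±7). It does not show that dosing starts after Visit 2.

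**Step 3: effect on the estimate if Table 4 is followed.** Let *d* be the true week-16 difference in 2-h PPG (exenatide minus insulin), *a* the between-arm difference in first-dose effect on the Visit 2 2-h value, and *b* the slope on baseline.
- Change score: estimate = *d* − *a*.
- Covariance model with the Visit 2 value as covariate: estimate = *d* − *b·a*.
- Within an arm: change is off by that arm's own first-dose effect.

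Statistical methods specifies a covariance model for efficacy endpoints and reports mean change within each group, so the second and third lines are the relevant ones. The article does not name the covariate; the Visit 2 value is assumed.

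The documents give no value for *d*, *a* or *b*. Purely for illustration, take *d* = −1.0 mmol/L and *b* from 0.3 to 0.7:

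| *a* (mmol/L) | Change score | Covariance model, *b* = 0.3 | *b* = 0.7 |
|---|---|---|---|
| +0.5 | −1.5 | −1.15 | −1.35 |
| 0 | −1.0 | −1.00 | −1.00 |
| −0.5 | −0.5 | −0.85 | −0.65 |
| −1.0 | 0.0 | −0.70 | −0.30 |
| −2.0 | +1.0 | −0.40 | +0.40 |

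Equal first-dose effects (*a* = 0) leave the between-arm contrast intact but still distort both within-group changes.

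**The case against.** The strongest reply is that the Visit 2 test was never meant to be done on study drug. PPG is described as seen at a pre-randomization visit, and Table 3 has no other meal test before the last visit. Stratification needs MAGE, so an allocated drug may not exist when Visit 2 begins. Table 4 is titled an overview, and the full protocol may hold visit-specific instructions. This is why the point is put as a conflict between sections and not as a fact about how patients were tested. It does not remove the conflict: the article prints a specific dosing step, applies the table to Visit 2, and nowhere says the step is skipped there.

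A reader might infer more than the documents support:

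- *All baseline meal-test values are on treatment.* The fasting sample precedes the dose; only the +120 min values are in question. Even for those, the text does not establish what sites did.
- *The Day 0 and Day 1 labels prove the conflict.* If dosing did start after Visit 2, nobody would be on drug at that test, which cuts against contamination.
- *The treatment effect shrinks by a known fraction.* That assumes both size and sign, and ignores the covariance model. If insulin's first dose lowers 2-h glucose more than exenatide's, the bias favours exenatide.
- *Baseline MAGE is compromised too.* The meal-test row does not show this, and stratifying on MAGE implies a recording obtained before allocation.

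The replies on severity also stand. Meal-test PPG, insulin and C-peptide are not among the Table 2 outcomes; PPG's standing rests on the blinding text.

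**Conclusion.** The point holds as a contradiction of moderate severity. Read at Visit 2, Table 4 makes the baseline +120 min glucose, insulin and C-peptide post-dose by about 120 to 150 min. That is incompatible with their use as baseline and with the implied pre-randomization measurement of PPG.

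If the table is followed, the between-arm result for 2-h PPG is biased by *a* for a change score or by *b·a* in a covariance model. The documents fix neither magnitude nor direction, and the illustrated range runs from no bias to a reversed sign. Within-group change is distorted in each arm by that arm's own first-dose effect.

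The exenatide timing discrepancy between Interventions and Table 4 is a separate inconsistency and does not itself show that baseline is affected.

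**What to change.** Reconcile Interventions, Table 3, Assignment of interventions, and Data collection and management (including Table 4):

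1. State the order of meal test, randomization and first dose at Visit 2, and whether Table 4's study-drug row applies there, so that the values analysed as baseline 2-h PPG, insulin and C-peptide are pre-treatment measurements.
2. The first participant was enrolled on 10 December 2015, so some tests may already be done. Establish from site records whether any Visit 2 test followed a dose. For those patients, do not use the Visit 2 +120 min value as baseline; compare week-16 values between arms instead. The Visit 2 fasting value, being pre-dose, and the stratification factors remain available for adjustment.
3. The sponsor should also reconcile the two statements on exenatide timing before meals, and the visit numbering (visit 6 against V9). No view is taken here on which timing is right.

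Items 1 and 3 cost a line or two of text each, with no extra visit or sample. Item 2 costs a check of dosing and sampling times. It cannot restore an untreated 2-h value for anyone already dosed.
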